## Abstract

**Background:**

Internalizing disorders such as anxiety and depression can be especially severe during adolescence, presenting significant challenges for affected individuals. While cognitive-behavioural therapy (CBT) has shown promise as an effective treatment for these conditions, a significant proportion of youth do not benefit sufficiently from CBT. One critical factor that may influence the effectiveness of CBT is adherence to therapy homework, with evidence suggesting a relationship between homework completion and therapy outcomes, including symptom reduction. In this context, smartphone apps have emerged as a potentially helpful tool to enhance adherence by providing engaging ways for adolescents to complete their therapy homework. However, in Germany, there is currently a lack of evaluated smartphone apps that can be deployed as adjuncts to CBT for adolescents.

**Method:**

This study is designed as a randomized controlled trial (RCT). It will evaluate the effects of the JAY smartphone app on therapy homework adherence during CBT for adolescents with internalizing disorders (*n* = 35) compared to CBT with standard paper-and-pencil homework (*n* = 35).

**Discussion:**

The findings of the JAY trial may contribute to the understanding of how smartphone apps can be integrated into CBT for adolescents to enhance therapy homework adherence and ultimately treatment outcomes.

**Trial registration:**

German Clinical Trials Register (DRKS) DRKS00026623. Registered on 13th October 2023, https://drks.de/search/de/trial/DRKS00026623/details.

**Supplementary Information:**

The online version contains supplementary material available at 10.1186/s13063-026-09806-0.

## Background

Anxiety and depressive disorders are highly prevalent during adolescence [1, 2], and the rates of these disorders have significantly increased as a consequence of the COVID-19 pandemic [3, 4]. They frequently co-occur and show a significant convergence of symptoms [5, 6]. Adolescents with anxiety or depressive disorders show lower social and academic functioning than unaffected peers [7, 8], and even more concerningly, have a higher risk of suicidality [9–11], which is a leading cause of death in young people [12]. The presence of affective disorders in adolescence and young adulthood further predicts poor health outcomes and functioning in adulthood [13, 14]. Considering the high prevalence and adverse impacts of these disorders, effective treatment for affected adolescents is crucial.

According to scientific consensus, cognitive-behavioural therapy (CBT) is the method of choice for treating anxiety and depressive disorders in both adults and youth (e.g., [15–17]). Nevertheless, a careful examination of the treatment effects of psychotherapy for depressed and anxious youth reveals only modest effect sizes. A significant proportion of affected youth are non-responders to therapy or continue to fulfill the criteria for a psychiatric diagnosis at the end of therapy [18–21]. Furthermore, findings regarding the long-term effects of CBT are mixed [15, 22].

The main influence of CBT lies in inducing cognitive and behavioural changes. This can be accomplished through cognitive restructuring as well as exposure and behavioural interventions [23]. One important component of CBT is therapeutic homework, which is a collective term to describe any activity that was developed within the session and should be completed by the patient between sessions. In the treatment of anxiety and depressive disorders, homework may include, in particular, journaling, exposure exercises in a natural setting, and activity scheduling [24]. Homework helps to generalize and maintain the skills acquired during therapy sessions [25, 26]. Moreover, patients are able to observe and document problematic situations throughout the week and bring them to the therapy session to discuss them with the therapist. Research in adults has shown that the amount of homework that patients complete and the quality of therapy homework adherence (THA) significantly predict treatment outcomes in terms of the reduction of anxiety and depressive symptoms (e.g., [27–29]). There is also evidence that this applies to adolescent patients with depression [30] but not for the treatment of adolescent anxiety [31].

In summary, THA is an important factor for treatment outcomes, with low THA potentially contributing to insufficient effectiveness of CBT. Indeed, studies have shown that low THA is a common phenomenon in cognitive therapy, especially in adolescents [32, 33]. For example, a study measuring homework compliance in adolescents with depression receiving CBT reported a homework completion rate of only 56%, and a decline during the therapy process was noted [34]. Non-adherence is influenced by patient, therapist, and task factors, but an empirical evaluation is impeded by various methodological difficulties [32, 35]. Nevertheless, some experience-based recommendations to improve THA can be made. For instance, homework should be meaningful, relevant to the central goals of therapy, salient to the focus of the session, agreeable to the therapist and patient, appropriate to the patient’s sociocultural context, doable, small, have a clear rationale and back-up plan, and should be practiced in session [36, 37]. It is also recommended that a time and place to complete the homework should be defined in advance [36, 37]. Accordingly, a qualitative study found that adolescent patients often perceive homework as too difficult or time-consuming and that they lack the motivation to complete it [38].

Smartphone apps may provide a way of improving mental health treatment in general and THA specifically [39–42]. Modern-day youth are growing up in an increasingly digital environment, gaining internet access at progressively younger ages [43]. Notably, around 96% of German adolescents aged 12–19 years have their own smartphone [44]. As such, mobile technology might represent a promising platform for enhancing mental health treatment [45].

In particular, smartphone apps can make psychoeducational content more accessible and facilitate in-the-moment self-assessments (such as documentation of thoughts and feelings), thus reducing recall bias. Moreover, they can support the practice of coping, relaxation, problem-solving skills, and exposure assignments. Mobile technology has certain advantages over paper-and-pencil-based homework. For instance, apps can respond adaptively to the patient’s input and give personalized feedback. They can send scheduled reminders in the form of push notifications and can include a display of progress as well as reward systems [46, 47]. The feature of in-the-moment assessments in natural settings, also known as ecological momentary assessment (EMA), might also enhance research on the feelings, thoughts, and behaviour of children and adolescents [48].

New apps are consistently being developed and introduced, and need to be scientifically evaluated in order to be used safely. Therefore, several (systematic and meta-) reviews have attempted to depict the current scientific basis of the employment of apps in the field of mental health. These reviews have analyzed apps used as an adjunct to psychotherapy [49] and stand-alone apps that are not integrated into face-to-face psychotherapy [50, 51]. Further research has focused on apps for youth and apps used in patients with anxiety or depression [52–55].

The functions of the apps analyzed in the reviews include monitoring symptoms (including mood, thoughts, and behaviour) as well as providing interventions, such as psychoeducation, exposure, response prevention, skills practice (e.g., mindfulness exercises), and promoting positive behaviours [53, 56, 57]. Monitoring functions are predominantly reported, with some apps even being limited to these functions [50, 54, 56]. The reviews show that most web or mobile apps are designed as stand-alone apps rather than serving as an adjunct to psychotherapy, despite the limitations of stand-alone apps [49, 50, 55]. Overall, the evidence on app usage seems to cautiously point in a positive direction, as most studies conclude that apps are safe, effective, easy to use, and well-received by patients and therapists in terms of acceptability and satisfaction [49, 55]. However, a decline in patient engagement over time has been noted, especially for assessment functions, albeit less so for adjunctive apps [49, 52, 55]. Adjunctive app use is also assumed to yield better longer-term outcomes [49, 50]. Monitoring activities seem to be undertaken more consistently via apps than on paper [56].

Although many apps claim to be based on CBT, the term is often used loosely and does not necessarily imply that an app draws on an evidence-based framework. Various authors have underlined that apps should be developed by trained psychologists and scientifically evaluated [49, 58].

A further important aspect to be considered is data privacy. Apps should not make patients’ data available to third parties, which would threaten confidentiality, and the transfer of data to the therapist should only take place with the patient’s informed consent [50, 56].

Overall, the reviews conclude that the evidence base for mobile apps is rather thin [52], especially regarding their use in child and adolescent psychotherapy [56]. Some apps lack any scientific evaluation, and high-quality studies such as randomized controlled trials (RCT) with active control groups are scarce [49, 52, 55], particularly in the case of adjunctive apps [49]. Furthermore, a more systematic investigation is needed to understand how smartphone technology provides therapeutic benefits. This includes examining common features of therapy apps, such as behaviour diaries, push notifications, and clinical information [59].

Research on app usage between therapy sessions and the effects of app usage on THA is even more scarce, even though it is recognized as having great potential [40, 46, 60]. Apps designed for adults that target THA include CBT MobileWork© for depression [61], CBT Assistant for social anxiety disorder [62], and PE Coach for post-traumatic stress disorder [63–65]. However, RCTs to prove the purported effects of these apps have yet to be conducted.

To the best of our knowledge, only one study to date has specifically explored the use of app-augmented CBT for the treatment of anxiety and depressive disorders in young individuals targeting THA [66]. In an ongoing multisite, randomized controlled pragmatic clinical trial, the authors are investigating the impact of a smartphone app on homework completion. They hypothesize that participants using the app-enhanced treatment will show higher homework compliance. Given the currently low compliance rates, the app is anticipated to have moderate effects. Since no results from this project were available at the time of our study protocol submission, we can only discuss aspects of the study design, such as sample size, without insights into the outcomes or effectiveness of the design.

Therefore, the purpose of this study is to address this research gap by evaluating a smartphone-enhanced CBT intervention designed for youth with various disorders, specifically focusing on anxiety and depressive disorders in this study, using a newly developed app (Journaling App for Youth, JAY) [67]. The primary aim of the JAY study is to investigate whether individuals who undergo a therapeutic intervention enhanced by smartphone usage show notably greater compliance in terms of both the (i) quantity and (ii) quality of completed therapy homework assignments compared to individuals who undergo a similar treatment without smartphone app support.

The following hypotheses will be investigated:The experimental group (CBT + JAY) will show a significantly higher overall THA score compared to the active control group (CBT) throughout the intervention phases, as assessed by quantitative aspects of therapy homework (relative ratio of completed and required entries) as well as qualitative aspects which together as a composite score constitute the primary outcome. The qualitative aspects (content fit, thoroughness, competence of behaviour/thoughts, and clinical relevance) will be evaluated by multiple independent raters using a rating system that defines the assessment criteria.The experimental group (CBT + JAY) will show higher THA compared to the active control group (CBT) as assessed using the clinician-rated Questionnaire for Therapy Adherence after each therapy session [68].The experimental group (CBT + JAY) will show a greater reduction in internalizing symptoms compared to the active control group (CBT) according to self-rating, as measured using the Internalizing Problems scale of the Youth Self-Report 11–18 (YSR/11-18R) [69, 70] as well as the self-report symptom checklists for anxiety (SCL-AD-S) and depression (SCL-DEP-S) from the “Diagnostic system for mental disorders based on ICD-10/DSM-5 for children and adolescents” (DISYPS-III) [71] and using an individual problem list.The experimental group (CBT + JAY) will show a greater reduction in internalizing symptoms compared to the active control group (CBT) according to caregiver rating, as measured using the Internalizing Problems scale of the caregiver-report Child Behaviour Checklist (CBCL/6-18R) [69, 70] as well as the caregiver-report scales for anxiety (SCL-AD-P) and depression (SCL-DEP-P) from the DISYPS-III [71].The experimental group (CBT + JAY) will show a greater reduction in internalizing symptoms compared to the active-control group (CBT) according to clinical rating, as assessed by a clinician using a structured clinical interview (ILF-INTERNAL) from the DISYPS-III [72].The experimental group (CBT + JAY) will show a stronger reduction in comorbid symptoms as measured using the scales Externalizing Problems and Total Problems of the self-report YSR/11-18R and the caregiver-report CBCL/6-18R [69, 70].Patients in the experimental group (CBT + JAY) will show a greater improvement in quality of life, sense of global self-worth, and emotion regulation strategies according to self-report compared to patients in the control group (CBT), as assessed by the Revised Questionnaire for Health-Related Quality of Life Assessment in Children (KINDL^R^) [73], by a modified German version of the Self-Perception Profile for Children called the Harter scale [74, 75], and by a modified version of the Questionnaire to Assess Children’s and Adolescents’ Emotion Regulation Strategies (FEEL-KJ) [76], respectively.Patients in the experimental group (CBT + JAY) will show greater treatment satisfaction than those in the control group (CBT), as measured by a modified version of the self-report Client Satisfaction Questionnaire (ZUF-8-M patient) [77, 78].

A comprehensive description of the clinical assessment tools mentioned above can be found in the “ Secondary outcomes” section. Additionally, the following research questions will be addressed:How feasible is the JAY smartphone app, and how satisfied are patients regarding its use?What are the clinical implications of symptom changes observed in the experimental group relative to those in the control group?Which moderators and predictors (such as gender and age) can be identified to predict treatment outcomes?

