### Eligibility criteria

Eligible participants will meet the following criteria: (1) adolescents aged between 13;0 and 17;11 years at T1; (2) diagnosed with one of the specified clinical conditions according to the 10th International Statistical Classification of Diseases and Related Health Problems (ICD-10) [79], including depressive episode (F32.0, F32.1, F32.8, F32.9), anxiety disorders (F40.00, F40.01, F40.1, F40.8, F41.0, F41.1, F41.2), emotional disorder with onset specific to childhood (F93.0, F93.2), and adjustment disorder (F43.2), as assessed by a clinician using a structured clinical interview (DISYPS-ILF INTERNAL) [72]; (3) self-reported internalizing symptoms with a clinically relevant score (*T* value ≥ 60) on the Internalizing scale of the YSR/11-18R [69]; and (4) willingness and ability to participate in the intervention, including sufficient German-language skills and smartphone competences demonstrated by the patient.

Patients will be excluded if any of the following exclusion criteria are met: (1) presence of autism spectrum disorder (F84) or another severe comorbid disorder identified as clinically predominant; (2) adolescent’s intelligence level below average (intelligence quotient (IQ) < 80), determined using a standard intelligence test (German version of the Culture Fair Intelligence Test (CFT 20-R) [80]); (3) critical escalations of symptoms indicative of the need for inpatient treatment; (4) concurrent participation in additional outpatient treatment; (5) indication for initiating new pharmacotherapy or adjusting the dosage of existing pharmacotherapy at the time of the intervention.

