#### Secondary outcomes

Secondary outcomes include:The quantity of therapy homework, as assessed by the relative ratio of completed to requested entries within the JAY app or on the paper-and-pencil sheets between the treatment sessions.Quality of the entries, as rated by a pool of clinicians based on the app entries or the homework sheets according to the rating system mentioned in the previous section.Patient-rated symptoms of anxiety and depression, assessed by the Internalizing Problems scale of the self-report YSR/11-18R [69, 70] as well as the self-report scales for anxiety (SCL-AD-S) and for depression (SCL-DEP-S) from the DISYPS-III [71]. Reliability and validity as well as sensitivity to change of the German version of the YSR/11-18R and the DISYPS-III scales have already been demonstrated in German samples [70, 71]. The Internalizing Problems scale of the YSR/11-18R will be assessed at every measurement time point and the SCL-AD-S and SCL-DEP-S will be assessed at T0 and T3.Caregiver-rated symptoms of anxiety and depression, assessed by the Internalizing Problems scale of the caregiver-report CBCL/6-18R [69, 70] as well as the caregiver-report scales for anxiety (SCL-AD-P) and for depression (SCL-DEP-P) from the DISYPS-III [71]. Reliability and validity as well as sensitivity to change of the German version of the CBCL and the DISYPS-III scales have already been demonstrated in German samples [70, 71]. The Internalizing Problems scale of the CBCL/6-18R will be assessed at every measurement time point, and the SCL-AD-P and SCL-DEP-P will be assessed at T0 and T3.Clinician-rated symptoms of anxiety and depression based on the ILF-INTERNAL from the DISYPS [72], assessed at T0 and T3.Individually defined problem behaviours were rated by the patients using an individual problem list (IPL) in every therapy session. The problem list allows for the assessment of four targeted issues, rated on a 5-point Likert scale, and of the burden of the problems, rated on a 10-point Likert scale. Individual problem lists have been shown to be reliable, valid, and sensitive to change [85].Patient- and caregiver-rated comorbid symptoms and overall behavioural and emotional problems, measured using the remaining scales Externalizing Problems and Total Problems of the self-report YSR/11-18R and the caregiver-report CBCL/6-18R [69, 70]. Reliability and validity as well as sensitivity to change of the German version of these scales have been demonstrated in German samples [70]. These outcomes will be measured at T0 and T3.Patients’ adherence during the weekly therapy sessions (e.g., engagement in tasks and activities) will be measured using the clinician-rated Adherence Questionnaire [68], which will be assessed after every therapy session. This was adapted from the AUTHARK trial [41], in which good internal consistencies were reported.Quality of life, assessed using the Revised Questionnaire for Health-Related Quality of Life Assessment in Children and Adolescents (KINDL^R^) [73], which evaluates aspects related to physical and psychological well-being, the adolescent’s self-worth, as well as friendships and family relationships. Reliability and validity as well as sensitivity to change of scale have been demonstrated in German samples [86, 87]. This outcome will be assessed at T0 and T3. Sense of global self-worth, assessed using a modified German version of the Self-Perception Profile for Children, called the Harter scale [74, 75], which evaluates perceptions of cognitive and physical competence, peer acceptance, physical appearance, and self-worth. Reliability and validity of the original scale were demonstrated in a German clinical sample [88]. This outcome will be assessed at T0 and T3. Emotion regulation strategies were assessed using a modified version of the Questionnaire to Assess Children’s and Adolescents’ Emotion Regulation Strategies (FEEL-KJ) [76], which evaluates adaptive and maladaptive strategies to regulate feelings of anxiety and sadness. Reliability and validity have been demonstrated [76]. This outcome will be assessed at T0 and T3. Retrospective mood assessments will be conducted in every week in which the patient has used the momentary assessment of the JAY app or the paper-and-pencil equivalent. All 16 momentary affective and mental states assessed during the week will be rated retrospectively for the same week on a scale from 0 to 100. Patient-rated satisfaction with the treatment, assessed using a modified version of the self-report Client Satisfaction Questionnaire (ZUF-8-M patient) [77, 78], which has been shown to be reliable, valid, and sensitive to change [89]. Satisfaction will be assessed once, at T3. Patient-rated usability of the JAY app, assessed using a German translation of the System Usability Scale (SUS), which has been shown to be reliable, usable, and valid [90]. The scale measures effectiveness, efficiency, and satisfaction of and with a system. Usability will be assessed for patients in the experimental group once, at T3. Life events in the domains of school, family, and friendships as well as illness, accidents, and losses, as measured by the Zurich Life-Event List (ZLEL), which has been shown to be reliable and valid [91]. This measure will be applied once, at the follow-up (T5) in this study.

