#### Predictors/moderators of treatment outcome regarding anxiety and depressive symptoms

The following variables will be evaluated as potential moderators or predictors of treatment outcomes for internalizing symptoms at T3: (1) sociodemographic variables (e.g., number of children in the family; socioeconomic status and place of residence; caregivers’ age, education, income, and occupation), which will be assessed through a caregiver questionnaire at T0, (2) severity of comorbid symptoms using the self-report YSR/11-18R and the caregiver-report CBCL/6-18R at T0 and T3 (see above), (3) patients’ specific psychological characteristics, such as intelligence, measured at T0 using the CFT20-R (see above).

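### Hypothesis 6 counts Total Problems as a measure of comorbid symptoms, although that overall score appears to include the internalizing problems already tested in hypotheses 3 and 4

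*Protocol article*

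**What the plan says.** All references are to the Protocol article.

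- **Background, hypothesis 6:** the app arm is expected to show a "stronger reduction in comorbid symptoms as measured using the scales Externalizing Problems and Total Problems of the self-report YSR/11-18R" and of the caregiver-report CBCL/6-18R. One construct, comorbid symptoms, is assigned two scales per informant.
- **Background, hypotheses 3 and 4:** the target construct, internalizing symptoms, is tested with the Internalizing Problems scale of the same YSR (self-report) and the same CBCL (caregiver report), alongside other instruments.
- **Secondary outcomes:** the scales of hypothesis 6 appear as "Patient- and caregiver-rated comorbid symptoms and overall behavioural and emotional problems, measured using the remaining scales Externalizing Problems and Total Problems" of the two forms, measured at T0 and T3. The Internalizing scales are measured at every time point.
- **Eligibility criteria:** patients must have "self-reported internalizing symptoms with a clinically relevant score" on the YSR Internalizing scale (T of at least 60).
- **Predictors/moderators of treatment outcome:** one candidate variable is "severity of comorbid symptoms using the self-report YSR/11-18R and the caregiver-report CBCL/6-18R", taken at T0 and T3. No scale is named.

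No section gives the item composition of Total Problems, removes internalizing content from it, or says whether one scale or both must improve for hypothesis 6 to be supported.

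**The concern.** A comorbidity measure should be able to stay still when only the target symptoms change. Externalizing Problems can do that. A score for the overall level of behavioural and emotional difficulties, taken from the same form that yields the Internalizing scale, by natural reading cannot: if internalizing symptoms fall and nothing else does, the overall score is expected to fall too.

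On that scale, hypothesis 6 partly repeats hypotheses 3 and 4. A favourable Total Problems result could be written up as reduced comorbidity when the only true effect is on the disorder being treated. The protocol gives little to correct such a misreading. According to the Participant timeline, comorbid conditions are assessed by questionnaire only, with no clinician interview, and the Discussion lists internalizing and comorbid symptoms as separate effects to be analysed.

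**Working it through.** The protocol states no figure for hypothesis 6, so there is nothing to reproduce. The check has a textual step and an illustration of size.

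**Step 1: the texts side by side.** Background attaches both scales to one construct, comorbid symptoms. Secondary outcomes attaches the same two scales to two constructs, comorbid symptoms and overall difficulties. An overall score that covers emotional problems in a trial of anxiety and depression covers the target problems. The second text is the better description, but it does not say which scale serves which construct, and it does not change the hypothesis.

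**Step 2: inputs for the illustration.**
- From the protocol: 35 patients per arm (Sample size).
- Assumed: Total Problems is the sum of an internalizing part I, an externalizing part E and other problems O; the treatment affects I only; every pairwise correlation is r = 0.2 to 0.6; the SDs of E and O are 0.7 to 1.5 times the SD of I (four pairs tried: 1 and 1; 0.7 and 0.7; 0.7 and 1; 1 and 1.5).
- Assumed: internalizing effect d_I = 0.3 or 0.5; a simple two-group comparison; two-sided 5% test; one informant.

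**Step 3: dilution of the effect.** With the SD of I set to 1 and those of E and O to s_E and s_O:

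d_T = d_I / √v, where v = 1 + s_E² + s_O² + 2r(s_E + s_O + s_E·s_O).

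- Least dilution (s_E = s_O = 0.7, r = 0.2): v = 1 + 0.49 + 0.49 + 0.4 × 1.89 = 2.736, √v = 1.654.
- Most dilution (s_E = 1, s_O = 1.5, r = 0.6): v = 1 + 1 + 2.25 + 1.2 × 4 = 9.05, √v = 3.008.

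**Step 4: probability of a favourable significant result on Total Problems.** Normal approximation: Φ(d_T·√(35/2) − 1.96), with √(35/2) = 4.183.

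| d_I | d_T, most to least dilution | Probability |
|---|---|---|
| 0.3 | 0.10 to 0.18 | 6% to 12% |
| 0.5 | 0.17 to 0.30 | 10% to 24% |

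Example: 0.5 / 1.654 = 0.302, and Φ(0.302 × 4.183 − 1.96) = Φ(−0.70) = 24%. With no effect anywhere, the rate in this direction is 2.5%.

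**Step 5: dependence on the decision rule.** A simulation of 20,000 trials per setting (equal SDs, r = 0.2 and 0.5) gave the following.
- *Externalizing alone:* two-sided rejection stays at about 5% (about 2.5% in the favourable direction) whatever the internalizing effect.
- *Both scales required:* the joint rate cannot exceed the Externalizing rate, so it is at most about 5%.
- *Either scale sufficient, d_I = 0.5:* 20% at r = 0.2 and 16% at r = 0.5, counting either direction. With d_I = 0 the corresponding rates are 9% and 8%, so part of the excess over 5% comes simply from having two tests.

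**The case against.** The strongest reply is that the protocol already handles this. Background refers the reader to Secondary outcomes for the full description of the instruments, and that section names two constructs and two scales. A sympathetic reader pairs Externalizing with comorbidity and Total with overall difficulties, so hypothesis 6 is only a compressed sentence. This stands in part: the pairing is possible and points to the remedy. But the section does not make the pairing, and the hypothesis as stated treats Total Problems as evidence on comorbidity.

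Other replies limit the point, and these stand:

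- **Size.** A reader might infer that the plan carries a known rate of false comorbidity findings. It does not. The SDs, correlations and effect sizes are all assumed, and the inflation needs a rule that Total Problems alone suffices, which the protocol does not state. The Discussion itself warns that the effective control condition may make the app's increment hard to identify, so d = 0.5 may be optimistic. A rejection on Total would also be a true finding on that scale; only its label would be wrong.
- **Mechanism.** A reader might infer that each raw point lost on Internalizing is lost on Total. That needs scoring rules which the protocol does not show. What it supports is overlap, inferred from its description and the scale's name.
- **Moderator analysis.** A reader might infer that the predictor of internalizing outcome already contains that outcome. The section names no scale, so this holds only if Total Problems is chosen.
- **Scope.** Hypothesis 6 is not redundant as a whole. Externalizing Problems is a separate scale, and a null result there beside a Total effect would itself be informative. The entry criterion on the Internalizing scale is not a defect.

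**Conclusion.** The point holds as a mismatch between construct and measure for one of the two scales in one secondary hypothesis. As worded, hypothesis 6 allows a fall in Total Problems to count as a fall in comorbid symptoms, while the protocol's own description of the scales implies that Total Problems includes the symptoms being treated.

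The conclusion rests on one inference, that the overall score includes internalizing content; no item list is given. The figures in the working show only that the spill-over is diluted, grows with the internalizing effect and depends on a decision rule left open. They are not estimates for this trial. The primary adherence outcome is untouched. The correction is still worth making because it changes what hypothesis 6 can conclude.

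**What to change.** 1. Reword hypothesis 6 so that the comorbidity conclusion rests on Externalizing Problems of the YSR and CBCL. Alternatively, use Total Problems with the internalizing part removed, if the scoring of the forms allows it.
2. Report Total Problems under its own label as overall symptom burden, and make Background and Secondary outcomes agree on which scale serves which construct.
3. If the predictor and moderator analysis takes comorbidity severity from the YSR and CBCL, name the same non-overlapping score there.

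The cost is wording: the scales concerned are already scheduled at T0 and T3. Externalizing Problems alone has a small drawback, since comorbid problems that are neither internalizing nor externalizing are left out. The reduced total keeps them but depends on scoring details to be checked in the manuals. The choice should be fixed before outcome data are analysed.
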